### 5. Meetings of the DSMC

The members of the DSMC will have one 'Formal Interim Analysis' meeting to review data relating to treatment efficacy, patient safety, and quality of trial conduct when 90-day follow-up data of 400 patients have been obtained. For details concerning this analysis please see sections 9 and 10 in this charter.

Based on the results of this first interim analysis, it is the DSMC's responsibility to decide if and when additional interim analyses are warranted. The DSMC may additionally meet whenever they decide and contact each other by telephone or e-mail to discuss evolving information from the trial.

### 6. Communication between the steering group and the DSMC

The DSMC will be blinded in its safety and efficacy data assessments. Data transferred to the DSMC will be aggregated according to treatment group and labelled as group A and group B. The DSMC can request unblinding from the steering group. The data transferred from the steering group to the DSMC will be prepared by an independent liaison, with assistance from the trial statistician, in a manner that allows all trial personnel to remain blinded.

The DSMC can request additional reports concerning outcome measures and complications at any time during the trial. The reports should be up-to date should be provided to DSMC within 1 week of the request.

### 7. Minutes of the DSMC meetings

The DSMC will prepare minutes of their meetings. The minutes will describe the proceedings at the meetings, including a listing of recommendations by the DSMC. Because the minutes may contain unblinded information, it is important that they are not made available to anyone outside the DSMC.

## 8. Recommendations to the steering group

After the interim analysis meeting, the DSMC will recommend that the steering group continue, hold or terminate the trial. This recommendation will be based primarily on safety and efficacy considerations and guided by statistical monitoring guidelines defined in this Charter and the trial protocol. Recommendations to amend the protocol or conduct of the trial made by the DSMC will be considered and accepted or rejected by the steering group. The steering group will decide whether to continue, hold or terminate the trial based on the DSMC recommendations. The DSMC will be notified of all trial protocol or conduct changes.

## 9. Statistical monitoring guidelines

The outcome parameters are defined in the REDUSE trial protocol. For the two groups, the DSMC will evaluate data on:

- The primary outcome measure - all cause mortality at 90 days
- The secondary outcome measures
  - Cognitive function measured using the Montreal Cognitive Assessment - BLIND (MoCA-BLIND) at 6 months
  - Health-Related Quality of Life using the European Quality of Life visual analogue scale (EQ-VAS) at 6 months.
  - Days alive and free of invasive ventilation within 90 days of inclusion.
  - Complications in the ICU (cerebral, cardiac, intestinal or limb ischemia or new onset severe AKI).
- Selected exploratory outcomes
  - Hyponatraemia ( $> 159$  mmol/L)
  - Acid base disturbances (hyperchloraemic acidosis [ $\text{pH} < 7.15$  and plasma  $\text{Cl}^- > 115$ ], Metabolic alkalosis [ $\text{pH} > 7.59$  and  $\text{S-BE} > 9$ ]).
  - Central venous catheter related complications that could potentially be related to concentrated drugs given in the intervention group (for example, thrombosis, stenosis, malfunction, and infection)
  - Severe hypoglycaemia ( $\leq 2.2$  mmol/l)
- Suspected unexpected serious adverse events (SUSAEs)

The DSMC will also be provided with these data.

- a. Number of patients randomised per intervention group (A, B) per site.
- b. Monitoring reports from respective centres

Based on evaluations of these data, the DSMC will decide if they want further data from the steering group and when next to perform analyses of the data. For the interim analysis, the data will be provided in one file as described below. The DSMC will use Lan-DeMets sequential monitoring boundaries, at the all interim analyses of the primary outcome measure, secondary outcomes. The DSMC will also assess if protocol specified event rates

are accurate. If not, the DSMC may suggest an adjustment of trial sample size or duration of follow-up to maintain power. The DSMC should be informed about all SUSACS occurring in the two groups of the trial within 3 days.

#### 10. Conditions for transfer of data from the steering group to the DSMC

The DSMC shall be provided with the data described below in one file. The DSMC will be provided with an Excel database containing the data defined as follows:

- Row 1 contains the names of the variables (to be defined below).
- Row 2 to N (where N-1 is the number of patients who have entered the trial) each contains the data of one patient.
- Column 1 to p (where p is the number of variables to be defined below) each contains in row 1 the name of a variable and in the next N rows the values of this variable.

The values of the following variables should be included in the database:

- A. PtID: a number that uniquely identifies the patient.
- B. Rdcode: The randomisation code (group A or B). The DSMC is not to be informed on what intervention the groups received.
- C. 1. EndInd: Primary outcome measure indicator (1 if patient fulfilled the primary outcome measure at day 90 and 0 if the patient did not).
- D. MoCA-BlindInd: Montreal Cognitive Assessment score at 6 months
- E. EQ-VASLInd: Health-Related Quality of Life at 6 months
- F. DAFInd: Day alive and free of mechanical ventilation
- G. ComplicationInd: Complications (1 if patient has had a complication as defined above during ICU stay and 0 if the patient did not).
- E. ExplorInd: Selected exploratory outcomes as defined above and SUSACS (1 if patient has had an exploratory outcome or SUSAC during ICU stay and 0 if the patient did not).
- F. GlulInd: Severe hypoglycaemia as defined above

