## 10.2 Analysis methods

Analyses will be performed according to an intention-to-treat principle. All analyses will be adjusted for site of admission. All analyses will be adjusted for site of admission. The primary outcome and the first secondary outcome (complications) will be analysed using mixed effects logistic regression with site as a random intercept. RR will be estimated using the 'nlcom' STATA command or G-computation in R (R Core Team, Vienna, Austria). Count data (mechanical ventilation-free days) will be analysed by van Elteren test with site as a covariate. Secondary continuous outcomes (MoCA-BLIND and EQ-VAS) will be analysed using mixed effects linear regression with site as a random intercept.

All primary conclusions will be based on our primary outcome and, a priori, secondary and explorative outcome results will be considered as hypothesis generating. Based on this we will consider a P-value of 0.05 as a threshold for statistical significance for all analyses.

All primary conclusions will be based on our primary outcome and, a priori, secondary and explorative outcome results will be considered as hypothesis generating. Based on this we will consider a P-value of 0.05 as a threshold for statistical significance for all analyses.

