#### Up to 90 days after inclusion

- Date of follow-up (dd-mmm-yyyy)
- Status (alive/deceased)
- Days alive and free of renal replacement therapy (RRT) (days; Only include full days without RRT. The data should be recorded for up to 90-days regardless of how the patient was discharged or readmitted.)
- Non-invasive and invasive mechanical ventilation-free days (days; Only include full days without invasive or non-invasive mechanical ventilation. Nasal high flow oxygen therapy is not considered mechanical ventilation. The data should be recorded for up to 90-days regardless of how the patient was discharged or readmitted)
- Vasopressor-free days (days) (Only include full days without vasopressors. The data should be recorded for up to 90-days regardless of how the patient was discharged or readmitted.)
- Days spent in any ICU (days) A day with any time spent in any (incl. non-REDUSE) ICU counts as an ICU day, even if it is less than 24 hours. The data should be recorded for up to 90-days regardless of how the patient was discharged or readmitted.)
- Hospital-free days (days; Only count full days out of hospital. Time spent in a rehabilitation facility, long-stay hospital, hospice, or nursing home is considered as time spent out of hospital. Includes any hospital (even non-REDUSE sites). The data should be recorded for up to 90-days regardless of how the patient was discharged or readmitted)
- ICU-free days (days)
- Creatinine at hospital discharge ( $\mu\text{mol/L}$ ; Latest value recorded within 90 days at any hospital)

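### The DSMC data file merges most safety outcomes into one flag and cannot show which patients have complete 90-day follow-up, so it does not support the review the charter assigns to it

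*Protocol*

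**What the plan says.** Section 9 of the DSMC charter (Appendix B) lists what the committee will evaluate by arm: 90-day mortality, the secondary outcomes, selected exploratory outcomes (a sodium disturbance above 159 mmol/L, two acid-base disturbances, catheter complications, severe hypoglycaemia) and SUSAEs. It applies Lan-DeMets boundaries to the primary and secondary outcomes. It also asks the committee to check the protocol's event rates, and lets it suggest a different sample size or follow-up duration.

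Section 10 of the charter then fixes the file that is to carry this review:
- Rows: "Row 2 to N (where N-1 is the number of patients who have entered the trial) each contains the data of one patient".
- EndInd, the primary outcome: "Primary outcome measure indicator (1 if patient fulfilled the primary outcome measure at day 90 and 0 if the patient did not".
- ExplorInd, covering the selected exploratory outcomes and SUSAEs: "1 if patient has had an exploratory outcome or SUSAC during ICU stay and 0 if the patient did not".
- The other columns are patient number, arm code (A or B), the two 6-month scores, days free of mechanical ventilation, the ICU-complication composite and severe hypoglycaemia. There is no column for site, for any date or for follow-up status.

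Charter section 5 triggers the formal interim when 400 patients have 90-day follow-up data, and Protocol section 14.3 describes it as covering the first 400 such patients. Protocol section 10.2 states: "All analyses will be adjusted for site of admission".

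Three smaller items stand in the same charter:
- Section 9 attaches the label "Hyponatraemia" to a value above 159 mmol/L, which Protocol section 3.3 and Appendix A call hypernatraemia.
- Section 9 monitors "Days alive and free of invasive ventilation within 90 days of inclusion", while Appendix A, for the 90-day data, says "Only include full days without invasive or non-invasive mechanical ventilation".
- Section 6 says "The DSMC can request unblinding from the steering group", although Protocol sections 5 and 5.4 list the steering group among those blinded.

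**The concern.** A DSMC can act only on what its file lets it see. Two features of this file stand in the way.

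First, a single yes/no flag for six kinds of event counts a patient once, whichever event occurred. An excess of one event in one arm can be diluted by a more frequent event, or offset by a deficit of another. Section 9 itself links catheter complications to the concentrated drugs given in the intervention arm, yet they have no column.

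Second, at the interim many rows belong to patients who have not reached day 90. EndInd has no value for them, and no date shows who they are. A statistician chosen by the DSMC would have to guess which rows belong to the interim set. The task most exposed is the event-rate check, because a misread mortality rate could lead to an unwarranted recommendation on sample size. Without a site column, the site-adjusted mortality model and the van Elteren test of Protocol section 10.2 cannot be run from the file either.

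**Working it through.** **Safety columns.** Section 9 against the columns of section 10:
- Hypernatraemia: ExplorInd only.
- Hyperchloraemic acidosis: ExplorInd only.
- Metabolic alkalosis: ExplorInd only.
- Catheter complications: ExplorInd only.
- SUSAE: ExplorInd only.
- Severe hypoglycaemia: ExplorInd and its own column.
- ICU complications: own column, a composite, as the secondary outcome is defined.

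Five of the six events in ExplorInd therefore cannot be separated. Appendix A records each of them separately in the daily data, so nothing new has to be collected.

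**Inputs for the mortality column.** Control mortality is 45%, the reduction 7.5 points (so 37.5%), alpha 5%, power 90%, total 1808 (Protocol section 10.1.1). The interim is at 400 patients with 90-day data (charter section 5). Accrual is 600 by the end of 2025 and 1200 by the end of 2026, so about 600 per year (sections 14.2 and 14.3).

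**The plan's own figure.** With a two-sided test and pooled variance,

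n per arm = [1.960 × √(2 × 0.4125 × 0.5875) + 1.2816 × √(0.45 × 0.55 + 0.375 × 0.625)]² / 0.075² = 903.3, rounded up to 904.

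The total is 1808, as stated.

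**Pending patients.** 600 × 90/365 = 148, so the file has about 548 rows, or 274 per arm (200 complete, 74 pending). At an assumed 400 or 800 per year it would have about 499 or 597 rows.

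**If pending patients were read as 0.** Let f be the share of their eventual 90-day deaths already recorded as 1 (an assumption). Apparent control mortality = (200 × 0.45 + 74 × 0.45 × f) / 274.
- f = 0, the worst case: 90/274, about 33%. The intervention arm shows 75/274 = 27.4%, so a 7.5-point difference appears as 5.5. At 400 or 800 patients per year the control figure is 36.1% or 30.1%.
- f = 0.70: (90 + 23.3)/274 = 41.4%.
- f = 0.85: (90 + 28.3)/274 = 43.2%.

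**The error can also run the other way.** Suppose early deaths are entered as 1 and pending survivors are left blank, and only filled cells are used. Control mortality is then (90 + 23.3)/(200 + 23.3) = 50.7% at f = 0.70, and (90 + 28.3)/(200 + 28.3) = 51.8% at f = 0.85.

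**Effect on the event-rate check.** The same formula with an apparent control rate of 32.8% gives a total of 1536 for the same absolute effect and 2954 for the same relative effect, against 1808. At 42.7%, inside the 41-43% range, it gives 1774 and 1974.

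**Effect on the efficacy decision.** Information is 400/1808 = 22%. With an O'Brien-Fleming-type spending function (an assumption; the protocol names only Lan-DeMets) the boundary is 1.960/√0.221 = 4.17. At the planned effect, Z is about 1.52 on the 400 complete patients and 1.40 in the worst case. Both lie far below the boundary.

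**The case against.** A reader might infer that the charter codes patients short of day 90 as survivors, so that the interim will report about 30% pooled mortality and 30% information (548/1808). The documents do not support that.
- Section 10 defines 0 as not having met the outcome at day 90, so a patient who has not reached day 90 fits neither code.
- Protocol section 6 has unobtainable data registered as missing.
- The same file holds 6-month scores that cannot yet exist for many patients, so it must allow blanks.
- Protocol section 14.3 limits the interim to the first 400 patients with 90-day data, and section 10.6 promises the DSMC data on survival.

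The low figures are a worst case under one misreading, not what the plan prescribes.

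Other points also soften the concern. SUSAEs go to the DSMC separately within 3 days. Severe hypoglycaemia and the complication composite have their own columns. The DSMC may ask for further reports at any time, to be supplied within 1 week, and receives randomisation counts per arm and site. The charter does not explicitly require the site-adjusted models at the interim.

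All of this stands and lowers the severity. It does not make the file adequate. Section 14.3 names a set of patients that the file gives no means of identifying. Counts per site do not attach a site to a patient. A committee can ask for a breakdown only if something prompts it, and a merged flag may give no prompt. The merging of events is the stated rule for ExplorInd, not an inference.

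**Conclusion.** The point holds in two parts. By its stated rule, ExplorInd hides five event types that section 9 says the DSMC will evaluate; this part needs no assumption. The file also lacks a not-due or missing code, dates and site, so the interim set cannot be identified, and site cannot be adjusted for, from the file alone.

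The mortality distortion is conditional. It arises only if pending rows are misread, and it rests on 600 patients per year and on the assumed share of deaths already recorded: about 33% against 45% at worst, 41-43% under the milder assumption. What is at risk is the event-rate check and any sample-size suggestion that follows from it. A changed efficacy decision is unlikely, given the assumed form of the boundary.

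The sodium label, ventilation wording and unblinding route are minor slips. The threshold, the protocol's outcome definitions and the existing independent liaison show how each can be settled. Overall this should be fixed before the interim, but it does not invalidate the trial's design or its final analysis.

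**What to change.** Amend charter sections 6, 9 and 10 as follows.
- Replace ExplorInd with one column each for hypernatraemia, hyperchloraemic acidosis, metabolic alkalosis, catheter complications and SUSAE, and keep the severe-hypoglycaemia column.
- Add site, randomisation date, and date of death or last known status.
- Code day-90 status as dead, alive, or not yet due or missing.
- State that the boundary and the event-rate check use only patients with known day-90 status. Define that set by randomisation at least 90 days before data cut, so that early deaths among pending patients do not enter without the matching survivors.
- Correct the sodium label to hypernatraemia.
- Reconcile the ventilation wording in charter section 9 with Appendix A and with the column in charter section 10.
- Route unblinding requests through the independent liaison already named in charter section 6.

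The cost is a charter amendment and a changed export. The safety items and dates are already collected, site is known from the randomisation, which is stratified by site, and neither recruitment nor the final analysis is affected.

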## Appendix C. Treatment algorithm for non-resuscitation fluids in the intervention arm.

[figure not shown]

### TREATMENT ALGORITHM FOR NON-RESUSCITATION FLUIDS – INTERVENTION ARM

Enteral nutrition: 2 kcal/ml, start according to local protocol.  
 Glucose solutions: 20% or higher concentration a).  
 Parenteral nutrition: according to local protocol.  
 Intravenous fluid and enteral water: given as needed to correct electrolyte disturbances, according to local protocol.  
 Medications and electrolytes: administer according to separate protocol.  
 Maintenance fluid: see flow chart below.

[figure not shown]

a) Administer ONLY in patients where enteral nutrition is not tolerated, earliest start 72 hrs after randomization. Maximum dose 1g/kg/day. Glucose solutions can be used earlier in patients at risk for hypoglycaemia (blood glucose < 5 mmol/l and trending downward).

b) Measured ins and outs:

Ins: nutrition, maintenance fluids, medications and electrolytes, blood transfusions, colloids.

Outs: diuresis, fluid removal from renal replacement therapy, tube drainage, vomiting/gastric tube drainage, bleeding, contents from faecal management system.

c) Overhydrated (increased total body water relative baseline) as suggested by weight above baseline/preadmission body weight, and/or peripheral/radiological oedema

d) Dehydrated (decreased total body water relative baseline) as suggested by body weight below baseline/preadmission body weight, decreased skin turgor and/or dry mucus membranes.

e) Maintenance fluid: intravenous fluid or enteral water prescribed to ensure that total volume of fluid covers basic need of water (approx 1 ml/kg/h).

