#### 5.2 Intervention

Participants will receive non-resuscitation fluids according to the protocol described below within two hours of randomization. Non-resuscitation fluids are defined as fluids other than colloids, blood products, or crystalloids administered to correct hemodynamic impairment as noted in the participants' charts. The type of maintenance fluids will be given according to usual care at each respective centre with the objective to use similar types of fluids in both groups. The allocated treatment will be continued while the participant is admitted in an ICU participating in the REDUSE trial up to a maximum of 90 days. Patients readmitted to an ICU

participating in the REDUSE trial within 90 days of inclusion will receive the same treatment to which they were initially allocated regardless of admission diagnosis.

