### 5.2.1 The intervention group

- Maintenance fluids will be discontinued in participants with a positive cumulative fluid balance who are judged not to be dehydrated by the treating physician.
- Glucose may be used at a maximal dose of 1g/kg/day using 20% or more concentrated glucose solutions starting at 72 h after inclusion as nutrition if enteral feeding is not tolerated. Glucose at this concentration or higher may be started earlier in patients at risk of hypoglycaemia (blood glucose <5 mmol/l and trending downwards) and in patients with insulin dependent diabetes if enteral feeding is not tolerated and if mandated by local protocol.
- Intravenous medications will be concentrated according to a trial specific protocol (Appendix D).
- Enteral nutrition will have an energy density of 2 kcal/ml and administered according to local protocols.
- Participants with neutral or negative cumulative fluid balance will receive maintenance fluids and other fluids such that the total dose covers their daily water need (about 1ml/kg/h).
- Intravenous fluid and enteral water will be used to correct electrolyte disturbances as needed.
- Parenteral nutrition will be given according to local protocol.

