### 5.2.2 Usual Care group

- Non-resuscitation fluids will be administered according to local routines.
- Unless the local protocols dictates otherwise, maintenance fluids (enteral water, crystalloids and/or glucose) will be given at 1 ml/kg/h.
- Unless local protocol dictates otherwise, a maximum glucose concentration of 10% will be used.
- Medications will be concentrated according to local protocol.

Site investigators will establish what constitutes usual care in their ICU prior to initiation of the trial. Site investigators will ensure protocol adherence in the two groups through continuous treatment monitoring.

Resuscitation fluids (albumin, blood products, crystalloids given to correct hemodynamic impairment as noted in patient chart or at a rate of  $\geq 5$  ml/kg/h if indication is unclear) will be administered according to local protocol (Finfer 2010). All other care will be according to local routines and not protocolized.

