##### 5.5.2. Fluid balance

Fluid balance is calculated as sum of all input of enteral and parenteral fluids minus all measured losses. Estimated loss through evaporation will not be included in fluid balance. Stool will not be included in balance unless the patient has a faecal management system or similar device in place.

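### Appendix C footnote b omits resuscitation crystalloid from the fluid inputs that section 5.5.2 counts; followed literally, it can give maintenance fluid that section 5.2.1 would stop

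*Protocol*

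**What the plan says.** Section 5.5.2, under the protocol's definitions: "Fluid balance is calculated as sum of all input of enteral and parenteral fluids minus all measured losses".

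Section 5.2.1 makes the cumulative balance the switch for maintenance fluid in the intervention arm. One side of the rule reads "Maintenance fluids will be discontinued in participants with a positive cumulative fluid balance who are judged not to be dehydrated by the treating physician". The other reads "Participants with neutral or negative cumulative fluid balance will receive maintenance fluids and other fluids such that the total dose covers their daily water need", with that need put at about 1 ml/kg/h.

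Appendix C carries the treatment algorithm for the same arm. Its footnote b spells out what is measured: "Ins: nutrition, maintenance fluids, medications and electrolytes, blood transfusions, colloids".

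Section 5.2 separates the fluid types: "Non-resuscitation fluids are defined as fluids other than colloids, blood products, or crystalloids administered to correct hemodynamic impairment". Section 5.2.2 names the same three kinds of resuscitation fluid, with albumin as the colloid.

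**The concern.** Footnote b includes two of the three kinds of resuscitation fluid (colloids and blood) and leaves out the third (crystalloid). It therefore does not set resuscitation fluid aside on principle. It simply gives a smaller input total than 5.5.2, short by the volume of resuscitation crystalloid.

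The switch in 5.2.1 depends on the sign of the balance, so an input total that is too small can turn a stop into a give. The crystalloid omission acts in one direction only: towards more fluid in the arm meant to receive less. Two things are at stake:

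- **Fluid separation.** The difference in volume between the arms is what the trial tests.
- **Adherence.** Section 5.5.3 counts departure from the treatment algorithm as a protocol deviation, and section 10 removes patients with a deviation from the per-protocol population. A patient treated by the literal footnote would be adherent by Appendix C and non-adherent by 5.2.1 read with 5.5.2.

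**Working it through.** The plan gives no figure to reproduce here. The check is a comparison of texts, followed by arithmetic on assumed volumes.

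**Step 1. Which inputs are counted.**

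| Input | Class (5.2, 5.2.2) | 5.5.2 | Footnote b |
|---|---|---|---|
| Colloids, including albumin | resuscitation | counted | listed |
| Blood products | resuscitation | counted | listed |
| Crystalloid for haemodynamic impairment | resuscitation | counted | **not listed** |
| Maintenance fluid | non-resuscitation | counted | listed |
| Nutrition, medications, electrolytes | non-resuscitation | counted | listed |

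No other listed item covers the gap. Footnote e confines maintenance fluid to fluid prescribed for basic water need, and the daily record in Appendix A keeps resuscitation and maintenance crystalloid under separate headings. The gap is narrower than all crystalloid, however. Appendix A classes crystalloid of unclear indication below 5 ml/kg/h as maintenance, which footnote b does count.

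**Step 2. When the decision changes.** Let B be the cumulative balance by footnote b, C the resuscitation crystalloid over the same period, and T the balance by 5.5.2. With outputs equal, T = B + C. In a patient who is not dehydrated, 5.5.2 says stop if T > 0, and footnote b says give if B ≤ 0. They differ exactly when −C < B ≤ 0.

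The footnote's outputs also lack the Appendix A item for other losses, L. With it, T = B + C − L. The two omissions pull in opposite directions. L is set to zero below.

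**Step 3. Illustration.** All volumes are assumed, none comes from the protocol. The patient weighs 80 kg. Day 1 has 1500 ml of inputs other than resuscitation crystalloid and 2000 ml out. Day 2 has 1200 ml of such inputs, 1500 ml out and no resuscitation fluid. Before any top-up:

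- B at end of day 1 = 1500 − 2000 = −500 ml
- B at end of day 2 = −500 + 1200 − 1500 = −800 ml

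| C on day 1 (ml) | T, end day 1 | T, end day 2 | By 5.5.2 | By footnote b |
|---|---|---|---|---|
| 0 | −500 | −800 | give | give |
| 500 | 0 | −300 | give | give |
| 1000 | +500 | +200 | stop | give |
| 2000 | +1500 | +1200 | stop | give |
| 3000 | +2500 | +2200 | stop | give |

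**Step 4. Volume when the decision changes.** Maintenance fluid only tops up the day's total, so the top-up is M = max(0, 24 h × 1 ml/kg/h × weight − all other fluid that day). The daily need is 1.44, 1.92 and 2.40 L at assumed weights of 60, 80 and 100 kg.

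- Day 2 of the illustration: 1920 − 1200 = 720 ml.
- Later days at 80 kg with 0, 0.5, 1.0, 1.5 and 2.0 L of other fluid: 1.92, 1.42, 0.92, 0.42 and 0 L.
- The day on which 1.0 L of crystalloid is itself given, at 80 kg with 0 and 0.5 L of other fluid: 0.92 and 0.42 L. It reaches zero once other fluid is 0.92 L.

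**Step 5. The excess limits itself.** Maintenance fluid is in the footnote-b inputs, so each top-up raises B towards the stop. Suppose outputs and other fluids are the same under both readings. The gap between them then widens only on a day when T > 0 under 5.5.2 and T ≤ C under footnote b. It is therefore below C before the top-up and below C + M after it. With C = 1.0 L and M = 0.72 L, that is below 1.72 L over the whole course.

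**The case against.** The strongest reply is that the correct rule is already in the protocol. Section 5.2.1 uses the term that 5.5.2 defines. The eCRF records resuscitation crystalloid and both daily and cumulative balance, and sections 6.1 and 8.2 require training in standardised recording of fluids. A site would have to set all this aside and follow a footnote that may be only an abbreviated list. The footnote itself speaks of measured ins and outs and does not mention balance. The flow chart it belongs to is not shown, so its use for the 5.2.1 switch is an inference. The algorithm also brings in hydration status: footnote c reads "Overhydrated (increased total body water relative baseline) as suggested by weight above baseline/preadmission body weight", with oedema as a further sign, and retained crystalloid would tend to show there.

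These points stand as limits on how often the conflict would matter. They do not remove it. The list is not marked as examples, and it belongs to the treatment algorithm for this arm.

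A reader might go further and infer that the intervention arm will be overtreated by a known volume, or that power is lost. The document supports neither. It gives no resuscitation volumes after randomisation and no distribution of balances, and the omission of other losses pulls the opposite way. Setting one assumed patient's top-up against the feasibility trial's median reduction would also compare unlike quantities. Damage to the per-protocol analysis is likewise only possible: it needs literal use of the footnote, a balance in the critical range, and a deviation judged against 5.5.2.

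Footnote a might be read as a second contradiction, because it lacks the early-glucose allowance for insulin-dependent diabetes in 5.2.1. That allowance is permissive, so following footnote a breaches nothing in 5.2.1.

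**Conclusion.** The inconsistency is real and plain in the text: footnote b and section 5.5.2 differ by the volume of resuscitation crystalloid. Read literally, footnote b gives maintenance fluid to a patient who is not dehydrated and has −C < B ≤ 0, where 5.2.1 with 5.5.2 would stop it. This conclusion assumes that the bedside balance is taken from footnote b, that hydration status does not override the sign, and that other losses do not cancel the omitted crystalloid.

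The frequency and the effect on the difference between arms cannot be derived, and the litre figures above are illustrations only. The consequence is weaker separation in some patients and an unclear standard for adherence. The primary intention-to-treat analysis, the sample size and the power calculations are untouched. It is a minor correction, but worth making because it sits in the operating instructions for the intervention arm.

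**What to change.** In Appendix C footnote b, replace both lists with *all ins and outs as defined in section 5.5.2*. This also settles other losses. Alternatively, add *crystalloids given for resuscitation* to the Ins. Reissue the chart to sites.

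Footnote a could be aligned with 5.2.1 on insulin-dependent diabetes at the same time, but this is optional.

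The cost is a footnote edit and redistribution of the chart. Nothing changes in data collection, sample size or analysis.
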